### Subgroup analyses

The effect of the treatment among different subgroups: (1) gender, (2) diabetes, (3) The European System for Cardiac Operative Risk Evaluation (EuroSCORE) II, (4) Cardiopulmonary Bypass (CPB) duration, (5) age, (6) high sensitivity C-reactive protein on POD 1 and (7) SOFA on POD 1 will be analyzed. Stratified analysis using a logistic regression or Cox proportional hazards model, as applicable, will be performed. By adding a product term to the model that already contains the treatment and the subgroup factor, the interaction between each subgroup factor and the treatment group will be tested.

## Discussion

In this prospective, single-center, randomized controlled trial, we will investigate whether GC, with a tapering dosage, could improve organ dysfunction measured by the SOFA score in patients with aTAAD undergoing surgery.

GC is commonly used in cardiac surgery with much controversy [18]. As abundant evidence has shown that patients with aTAAD developing SIRS are more likely to suffer negative consequences, looking for novel effective treatments in this patient population to regulate such a pathophysiological process may be of paramount importance [19]. Previously, randomized controlled trials (RCTs) have emphasized on the clinical impact of intraoperative GC without considering postoperative inflammation control in cardiac surgery. Instead, in our study, sequential usage of GC will be achieved at a dosage that is widely used to treat acute severe inflammation-related conditions. Although the duration is relatively short (3 days), it fits in the clinical context and guarantees the feasibility of the study because some stable patients may leave ICU in 3 days. In addition, choosing indicators (SOFA Score) reflecting organ dysfunction increases the clinical value of the research. Data from the International Registry of Aortic Dissection has shown that organ failure is one of the leading causes of death in patients with aTAAD [1]. Examining the influence of GC with respect to the SOFA score could address this clinical quandary and potentially enhance patient survival rates.

There are a variety of strengths in our study. 1) The effect of GC in patients with aTAAD undergoing surgery is lacking, especially for those undergoing total aortic arch replacement with frozen elephant trunk implantation. Such a patient population is greatly exposed to the risk of SIRS and subsequent deterioration in organ function. This study will be the first RCT to investigate the role GC could play in these patients. 2) Former interventions of GC in cardiac surgery generally adopted a pulse regimen without tapering [7, 20]. The dosage of GC was particularly high (eg. 1 g MP) when given prophylactically before the initiation of CPB. However, benefits of GC to regulate dysregulated inflammation have mostly been observed in critical care studies adopting a mild-to-moderate dose of GC, as we have seen in inflammation-mediated conditions, such as acute respiratory distress syndrome [21–23]. In our study, we will implement an initial dosage of 4 mg/kg/d MP on POD 1 and taper it to 1 mg/kg/d on POD 3. Such a regimen will provide novel evidence on whether sequential and tapered use of GC would be better for patient prognosis. 3) A reduction in the SOFA is a reliable indicator of improvement in organ function and survival potential. Organ failure is one of the most prominent causes of death in surgical patients of aTAAD based on the data from international registry. Unfortunately, accurate definition of organ dysfunction is relatively missing, especially when multiple organs are involved. Previously, we have demonstrated that the SOFA score is associated with and could be used as a good predictor for all-cause in-hospital mortality and a lower SOFA score is linked to a decreased possibility of death after surgery, especially the one on POD 2 and POD 3 [17]. As our primary outcome would look at the difference between the SOFA score on POD 1 and POD 4, we believe such a choice could further elucidate the clinical value of the SOFA score. 4) Multiple biomarkers, such as CRP and IL-6, will be recorded in the research, which has the potential not only to depict a more accurate picture of inflammatory state in patients with aTAAD, but also to monitor and compare the effect of GC on inflammation as part of our secondary outcomes.

At the same time, it should be noted that several limitations may exist. First, as a single-center study, variations between different centers and clinical practice will not be considered, which may restrict the validity of the result in certain clinical and social context. Secondly, intraoperative GC will not be included as part of the research protocol as our current trial members work independently from the anesthesia team. As a result, the majority of patients will receive GC before the initiation of CPB even if they will be randomized to the control group in this study. However, it will still be comparable as patients in the control group will be free from sequential and tapering usage of GC postoperatively.

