#### Exclusion criteria

1. Iatrogenic aortic dissection;2. History of bacterial or fungal infections within the past 30 days;3. History of GCs or anti-inflammatory drug use within the previous 14 days;4. Allergy to GCs;5. Pregnancy;6. Cushing's syndrome or Addison's syndrome;7. History of implantable cardioverter defibrillator or permanent pacemaker implantation;8. Patients with malignancies undergoing chemotherapy, immunotherapy or targeted therapy;9. Patients with severe preoperative hepatic insufficiency;10. Patients with severe preoperative renal insufficiency;

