**Fig. 2 Fig2:**
[figure not shown]
Diagram of interventions

The first dose of MP will be given on the morning of postoperative day (POD) 1 at a dosage of 2 mg/kg/d, followed by another dose with the same dosage 12 h later. On POD 2 and POD 3, MP will be reduced to 1 mg/kg/d and 0.5 mg/kg/d respectively, with 12 h intervals between two injections.

All patients in the control group will receive treatments as usual without the administration of GC. Patients will be required to be supervised by medical personnel when administering the study drug, and their vital signs will be checked regularly in case of emergency.

Strategies to improve adherence to intervention and monitor adherence to procedures will be implemented. Three dedicated research fellows will screen all patients who enter the ICU after surgery. They will be responsible to check if certain candidate meets the study criteria. They will also be in charge of ensuring that intervention will be prescribed based on the protocol. In addition, two independent intensive care specialists will monitor adherence to interventions throughout the study period.

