### ***Data to be collected*** (Table 1)

**Table 1 Tab1:** Data to be collected

Time Points	Day of ICU admission	Treatment					
		Preoperative	Pre-drug	24 h	48 h	72 h	Discharge or death
Enrollment	x						
Informed consent	x						
Inclusion and exclusion criteria	x						
Demographics^a^	x						
Past medical history^b^	x						
Pre-operative cardiac function^c^	x						
Operative information^d^	x						
Assessment							
Temperature		x	x	x	x	x	
Respiratory rate		x	x	x	x	x	
Heart rate		x	x	x	x	x	
Systolic blood pressure		x	x	x	x	x	
Diastolic blood pressure		x	x	x	x	x	
SOFA score	x			x	x	x	
Methylprednisolone administration				x	x	x	
Inflammatory indicators^e^		x	x	x	x	x	
Blood count^f^		x	x	x	x	x	
Blood biochemistry^g^		x	x	x	x	x	
Arterial blood gas^h^		x	x	x	x	x	
Concomitant medications^i^		x	x	x	x	x	
Adverse events^j^				x	x	x	x
24 h fluid intake and output		x	x	x	x	x	

*TIA* Transient ischemic attack, *COPD* Chronic obstructive pulmonary disease, *DM* Diabetes mellitus, *NYHA* New York Heart Association, *LVEF* Left ventricular ejection fractions, *TAPSE* Tricuspid annular plane systolic excusion, *ECG* Electrocardiogram, *ALICE* Albumin-indocyanine green evaluation, *ICU* Intensive care unit, *CCB* Calcium channel blockers, *CRP* C-reactive protein, *PCT* Procalcitonin, *ESR* Erythrocyte sedimentation rate, *TNFα* Tumor necrosis factor-α, *IL-6* Interleukin-6, *IL-10* Interleukin-10, *pH* potential of Hydrogen, *CRRT* Continuous renal replacement therapy

^a^age, sex, height(cm), weight(kg), smoking and alcohol consumption

^b^pre-existing definite preoperative diagnosis; previous or screening period medical history (including at least hypertension, TIA, COPD, stroke, DM, various arrhythmias, peptic ulcer)

^c^preoperative NYHA classification, preoperative cardiac ultrasound including LVEF, TAPSE, preoperative ECG, myocardial enzyme profile, preoperative ALICE score for entrapment

^d^name of the procedure, duration of the procedure (min), time outside the body (min), time of block (min), time of transfer to the ICU. Intraoperative dose and time of hormone use, blood loss, and transfusion volume; β-blockers, CCB, anticoagulants such as aspirin, antiplatelet agents, antihypertensive agents, cardiotonic agents, proton pump inhibitors or H2-blockers, antibiotics used within the previous 7 days

^e^CRP, PCT, ESR, TNFα, IL-6, IL-10

^f^hemoglobin, white blood cell, neutrophil count, lymphocyte count, platelet count

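### The control arm is described as care without glucocorticoids, but most patients in both arms receive them before bypass: the trial tests an add-on, and the recorded exposure is absent from the stated primary comparison and subgroup list

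*Protocol article*

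**What the plan says.** The protocol article describes the comparator in two ways.

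- **Intervention** (text under Fig. 2): "All patients in the control group will receive treatments as usual without the administration of GC".
- **Discussion**, limitations paragraph: GC given during the operation lies outside the trial's control, because anaesthesia is run by a separate team. The authors therefore expect that "the majority of patients will receive GC before the initiation of CPB even if they will be randomized to the control group". Their defence of the design is that "it will still be comparable as patients in the control group will be free from sequential and tapering usage of GC postoperatively".

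The exposure is to be recorded. Footnote d of Table 1 (Data to be collected) lists "Intraoperative dose and time of hormone use, blood loss, and transfusion volume" among the operative information. I read hormone here as glucocorticoid.

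The stated analyses do not name it. Data analysis gives a t-test or Wilcoxon test between the two groups. Subgroup analyses lists seven factors with interaction terms: gender, diabetes, EuroSCORE II, bypass duration, age, "high sensitivity C-reactive protein on POD 1", and SOFA on POD 1. Randomization and blinding gives blocks of 4 and mentions no stratification.

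Exclusion criterion 3 bears on the same exposure: "History of GCs or anti-inflammatory drug use within the previous 14 days". It makes no statement about GC given during the index operation.

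**The concern.** A reader who takes the comparator from the Intervention section will read the result as GC against no GC. By the article's own account that contrast exists only in the minority who had none before bypass. In the rest, both arms have had GC and the trial compares continuing with not continuing.

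The article itself gives a reason to think that the two situations may differ. Its Introduction says that prophylactic bolus GC may regulate inflammation at the cost of adrenal-axis suppression, and the Discussion presents the tapered regimen as a departure from that practice. Yet the prophylactic dose is the background treatment of most participants. What is at stake is the scope of the conclusion. A positive or null result applies to the add-on question, and a reader of the trial report will need to know how many patients in each arm had prior GC.

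**Working it through.** **1. The passages side by side**

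| Point | Where | Content |
|---|---|---|
| Comparator | Intervention | usual treatment, no GC |
| Background GC | Discussion, limitations | majority of patients, both arms, before bypass, outside protocol control |
| Timing of screening | Intervention | on ICU entry, after surgery |
| Exposure recorded | Table 1, footnote d | intraoperative dose and time |
| Primary comparison | Data analysis | unadjusted two-group test |
| Subgroup factors | Subgroup analyses | seven, this one not among them |
| Recent GC use | Exclusion criteria, item 3 | excluded within 14 days, intraoperative use not addressed |

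The first two rows agree only if the Intervention wording is read as postoperative GC. Because screening follows surgery, the exposure is fixed before randomisation and is balanced between arms in expectation. Item 3, read literally, would exclude the majority that the limitations paragraph describes, so these passages also need to be reconciled.

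**2. The plan's own figure**

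Inputs from Sample size: decline 2.87, SD 1.69, 25% greater reduction, two-sided α = 0.10, power 0.90.

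- δ = 0.25 × 2.87 = 0.7175.
- n per arm = 2 × [1.69 × (1.645 + 1.282) / 0.7175]² ≈ 95.0, rounded up to 96. Total 192, and 192 × 1.10 = 211.2, rounded up to 212. The stated figures reproduce.
- Power at 96 per arm = Φ(0.7175 / (1.69 × √(2/96)) − 1.645) = Φ(2.94 − 1.645) = 0.90.

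**3. What dilution would look like, if there is any**

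The article gives no share exposed and no effect by exposure, so both are assumptions here. Let *m* be the share given intraoperative GC and *r* the fraction of 0.7175 kept in those patients, with the full 0.7175 in the unexposed. Average effect = 0.7175 × (*m* × *r* + 1 − *m*). Power is at 96 per arm and α = 0.10.

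| *r* | *m* = 0.51 | *m* = 0.75 | *m* = 0.90 |
|---|---|---|---|
| 1 | 0.718, power 0.90 | 0.718, power 0.90 | 0.718, power 0.90 |
| 0.75 | 0.626, power 0.82 | 0.583, power 0.77 | 0.556, power 0.74 |
| 0.5 | 0.535, power 0.71 | 0.448, power 0.58 | 0.395, power 0.49 |

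Only the top row applies if there is no effect modification. It also applies if the 25% is already an average over this centre's usual mix of patients.

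**4. What an interaction test could show**

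SE of the difference in effects = 1.69 × √(2/(96*m*) + 2/(96(1 − *m*))). With *r* = 0.5 the difference is 0.359.

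- *m* = 0.60: SE 0.498, power Φ(0.359/0.498 − 1.645) = 0.18.
- *m* = 0.75: SE 0.563, power 0.16.
- *m* = 0.90: SE 0.813, power 0.11.

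At the α = 0.05 named in Data analysis these become 0.11, 0.09 and 0.06. Even with no effect at all in exposed patients (*r* = 0), power at α = 0.10 is only 0.42 to 0.22 over the same range.

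**The case against.** The best defence is that nothing is hidden and nothing is biased. The aim in the Introduction names postoperative GC with a tapering regimen and sets no comparator of no GC. The sentence in the Intervention section stands among the postoperative dosing instructions and can be read that way. The limitations paragraph discloses the exposure, explains why it lies outside the protocol, and already describes the contrast as postoperative. A randomised add-on to usual care gives a valid average effect, and covariates and further subgroups are often left to an analysis plan, which is not shown here.

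Most of this stands. A reader might infer that background GC makes the arms non-comparable. It does not, because it is given before randomisation. A reader might also infer that the trial is underpowered because of it. The documents do not show that: the 25% is assumed for the GC group as a whole, and the 2.87 comes from the centre's own patients, who may have had the same intraoperative GC. Nor would a subgroup test rescue a null result, as its power shows.

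Two things remain. The Intervention wording, taken literally, conflicts with the limitations paragraph. And the article does enumerate its subgroup factors, and the list leaves out a recorded pre-randomisation exposure to the same drug class. CRP and SOFA on POD 1 are measured after surgery and may partly reflect that exposure, but they do not stand in for it. The planned summary of baseline characteristics could include it, but the article does not say so.

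**Conclusion.** The point holds as one of labelling and of an unused covariate. The trial estimates the effect of postoperative tapered GC on top of usual perioperative care that mostly includes intraoperative GC. The control description should say so, and the conclusion should be limited to that contrast.

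No numerical loss can be attached to it. Power anywhere between 0.90 and 0.49 is compatible with the assumed ranges above (51% to 90% exposed, all to half of the effect retained), and the top of that range is as consistent with the documents as the bottom. The stronger readings, that the comparison is biased, that dilution is established, or that the question was silently changed, are not supported. This verdict assumes that randomisation always follows the operation, as screening on ICU entry implies.

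**What to change.** 1. Reconcile the control description in the Intervention section with the limitations paragraph of the Discussion, and state how exclusion criterion 3 treats intraoperative GC.
2. Word the comparator and the conclusion as postoperative tapered GC versus none, on top of usual perioperative care that may include intraoperative GC.
3. Report intraoperative GC (given or not, dose, time) by arm with the baseline data.
4. Add it as a baseline covariate in an adjusted analysis of the SOFA difference, beside the planned two-group test.
5. Add it to Subgroup analyses as an eighth, explicitly exploratory interaction factor, fitted for the primary outcome in a linear model. Report the estimates with intervals in exposed and unexposed patients.

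The cost is text and one or two model terms, since Table 1 already calls for the data. The downside is one more interaction test with low power, less still if few patients are unexposed. It should be presented as descriptive and not used by itself to explain a null result.

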## Data Availability

Data sharing is not applicable to this article as no datasets were generated or analysed for this study protocol.

## Abbreviations

aTAAD: Acute Type A aortic dissection
SIRS: Severe inflammatory response syndrome
IL: Interleukin
GC: glucocorticoid
DECS: Dexamethasone for Cardiac Surgery
GLAD: Glucocorticoids in Patients with acute type A Aortic Dissection
ICU: Intensive care unit
POD: Postoperative day
MP: Methylprednisolone
SOFA: Sequential organ failure assessment
CPB: Cardiopulmonary bypass
CRP: C-reactive protein
